### Data collection and monitoring

2.9

Data collection will encompass a range of patient characteristics, including age, height, weight, body mass index (BMI), ASA score, drinking status, smoking status, parity, duration of surgery, intraoperative bleeding, and intraoperative analgesia grade. All pertinent data will be meticulously recorded in case report forms (CRFs) and subsequently inputted into an electronic database under the vigilant supervision of the principal investigator (Table 1). An independent Data Monitoring Committee (DMC) will be tasked with the ongoing oversight of the data collection process. Upon completion of data registration, the electronic database will be safeguarded. De-identified datasets will then be forwarded to an independent statistician for comprehensive analysis in accordance with a predefined statistical plan. Any serious adverse events (SAEs), whether or not they are related to the study medication (e.g., persistent hemodynamic instability), must be promptly reported to the principal investigator. In such instances, the perioperative care team is obligated to implement necessary measures to safeguard participant wellbeing. Furthermore, these SAEs must be communicated to the DMC within a 24-h window for thorough discussion and to determine if any adjustments to the study interventions or the study’s discontinuation are warranted.

**Table 1 tab1:** Schedule of patient enrolment, study interventions and outcome assessment.

	Study period							
	Enrollment	Allocation	Post-allocation					Close-out
Time point	Pre-op visit	Pre-op 1 day	0 h post-op	12 h post-op	24 h post-op	48 h post-op	72 h post-op	Discharged
Patient enrolment								
Eligibility criteria	×							
Written informed	×							
Consent								
Demographic data	×							
Baseline characteristics	×							
Randomization/allocation		×						
Study interventions								
Liposomal bupivacaine			×					
Ropivacaine & PCIA			×					
PCIA			×					
Outcome assessment								
VAS pain score during turning over				×	×	×	×	
VAS pain score at rest				×	×	×	×	
QoR-15 scale					×	×		
Need for rescue analgesia				×	×	×	×	
VAS anxiety score							×	
NRS sleep score					×	×	×	
Maximum walking duration					×	×	×	
NRS for satisfaction with analgesic					×	×	×	
Opioid consumption								×
Length of hospital stay								×
Nausea			×	×	×	×	×	
Vomiting			×	×	×	×	×	
Adverse events								
Allergy			×	×	×	×	×	
Wound infection			×	×	×	×	×	
Lightheadedness			×	×	×	×	×	
Headache			×	×	×	×	×	
Circumoral numbness			×	×	×	×	×	
Tongue paresthesia			×	×	×	×	×	
Drowsiness			×	×	×	×	×	
Irritability			×	×	×	×	×	
Hypotension			×	×	×	×	×	
Hypertension			×	×	×	×	×	
Hypoventilation			×	×	×	×	×	
Bradycardia			×	×	×	×	×	
Tachycardia			×	×	×	×	×	
Arrhythmia			×	×	×	×	×	
Cardiac arrest			×	×	×	×	×	

According to SPIRIT, statement of defining standard protocol items for clinical trials.

Pre-op, preoperative; Post-op, postoperative; QoR-15, patient self-assessment of Quality of Recovery-15 scale; VAS, visual analogue scale; NRS, numerical rating scale; PCIA, patient-controlled intravenous analgesia pump.

### Sample size calculation

2.10

Based on previous studies (21–23), a minimum change of at least 1.40 in the VAS pain score is considered to be clinically significant, denoting a substantial alteration in pain perception. The standard deviation (SD) of 1.55, derived from these studies, quantifies the variability in pain measurements. Using a two-sided significance level (*α*) of 0.05 and a desired statistical power of 80%, the initial sample size calculation based on a *t*-test indicated that a minimum of 20 participants per group would be necessary to detect a clinically significant change. This calculation assumed a single measurement per patient. However, the primary analysis includes 4 repeated measurements per patient, which increases the statistical power. To account for the correlation among repeated measures, we incorporated an intraclass correlation coefficient (ICC) of 0.53 into the sample size calculation. Additionally, to address multiple pairwise comparisons among the three study groups, we applied the Bonferroni correction, adjusting the significance level from 0.05 to 0.017 (0.05/3). The final sample size was calculated using the following formula for repeated measures: The formula is 
$n=\frac{{\left(Z1-\alpha /2+Z1-\beta \right)}^{2}\times (1+(\kappa -1)\rho )\times \sigma^{2}}{\Delta^{2}\times (1-\rho )}$
 (*n* is the sample size required per group, 
κ
 is the number of repeated measurements (4 in this study), 
σ
 is the standard deviation (1.55), 
Δ
 is the minimal clinically important difference (1.40), and 
ρ
 is the intraclass correlation coefficient (0.53). After adjusting for repeated measures, Bonferroni correction, and an anticipated dropout rate of 10%, we determined that a sample size of 67 participants per group would be required. Therefore, we plan to enroll a total of 201 patients (67 per group).

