### Primary outcome

2.4

The primary outcome is postoperative pain intensity, assessed using the Visual Analogue Scale (VAS) during standardized movement (instructing patients to turn over) at 12, 24, 48, and 72 h post-surgery. The VAS pain score ranges from 0 (indicating no pain) to 10 (indicating intolerable pain) points. In this longitudinal analysis, a generalized estimating equation (GEE) model with exchangeable correlation structure will be employed to evaluate overall differences in pain scores among groups across the four predefined postoperative intervals.

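### The printed repeated-measures formula does not match the stated primary contrast and does not yield 67 per group; the error is conservative, so the trial is overpowered for 1.40 points

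*Protocol article*

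**What the plan says.** Section 2.10 (Sample size calculation) takes its planning difference from cited studies: "a minimum change of at least 1.40 in the VAS pain score is considered to be clinically significant". On spread it says: "The standard deviation (SD) of 1.55, derived from these studies, quantifies the variability in pain measurements". A two-sided t-test at 0.05 with 80% power and one measurement per patient "indicated that a minimum of 20 participants per group would be necessary".

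The section then adds three elements: four measurements per patient with an intraclass correlation of 0.53, a Bonferroni level of 0.017 for three pairwise comparisons, and 10% dropout. On the first it states: "However, the primary analysis includes 4 repeated measurements per patient, which increases the statistical power". It continues: "The final sample size was calculated using the following formula for repeated measures". The formula printed there is

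n = (Z1−α/2 + Z1−β)² × (1 + (κ−1)ρ) × σ² / [Δ² × (1−ρ)],

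with n defined as the number per group. The section concludes with 67 per group, 201 in total.

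Section 2.4 (Primary outcome) describes the analysis that this n should serve: a GEE with exchangeable correlation to "evaluate overall differences in pain scores among groups across the four predefined postoperative intervals".

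**The concern.** Section 2.10 says that repetition adds power, but its formula makes n grow with the number of measurements. The factor (1 + (κ−1)ρ) is the design effect for κ correlated observations counted as separate units. It becomes the variance factor for a patient's mean only after division by κ, and that division is absent. The factor 2 that any difference between two independent groups needs is also absent, and the divisor (1−ρ) has no counterpart in the variance of a time-averaged difference.

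The number and its derivation are therefore both in doubt. The sample size for the primary outcome would have no valid basis as printed, and a reader could not tell what difference the trial can detect. This matters for interpretation because section 2.11 judges results by p-values and does not refer back to the 1.40-point threshold.

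**Working it through.** **Inputs, all from section 2.10:** Δ = 1.40, σ = 1.55, κ = 4, ρ = 0.53, 80% power, two-sided α = 0.05 (0.017 or 0.05/3 after Bonferroni), dropout 10%. The contrast is taken from section 2.4.

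Write f = (Z1−α/2 + Z1−β)² × σ²/Δ², with σ²/Δ² = 2.4025/1.96 = 1.226.

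**1. The plan's first figure.** For one measurement at two-sided 0.05, n = 2f = 19.2, so 20 per group. This reproduces.

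**2. The plan's final figure.** The repeated-measures factor in the printed formula is (1 + 3 × 0.53)/(1 − 0.53) = 2.59/0.47 = 5.51.

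| Quantile used in the printed formula | n | Rounded up | After 10% dropout |
|---|---|---|---|
| Two-sided 0.017 (as stated) | 70.4 | 71 | 71/0.9 → 79 |
| Two-sided 0.05/3 | 70.7 | 71 | 79 |
| Two-sided 0.05 | 53.0 | 54 | 60 |
| One-sided 0.017 | 59.3 | 60 | 60/0.9 → 67 |

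Of these, only the one-sided quantile gives 67, against the stated two-sided level and the printed Z1−α/2. A different expression, 2f(1 + 3ρ) with no (1−ρ) and no dropout, gives 66.2 to 66.5 and so also rounds to 67, but it is not the printed formula. The article does not show which route was taken.

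**3. The formula for the stated contrast.** Under exchangeable correlation, the mean of κ measures in one patient has variance σ²[1 + (κ−1)ρ]/κ. A difference between two groups of size n has twice that variance divided by n. Hence

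n = 2(Z1−α/2 + Z1−β)² σ² [1 + (κ−1)ρ] / (κΔ²).

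At two-sided 0.05/3: 2 × (2.394 + 0.842)² × 2.4025 × 2.59 / (4 × 1.96) = 16.6, so 17 evaluable and 17/0.9 → 19 enrolled per arm.

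**4. Size of the discrepancy.** Printed over correct is 5.51 / (2 × 2.59/4) = 5.51/1.295 = 2/(1−ρ) = 4.26. Going from κ = 1 to κ = 4 multiplies n by 2.59 in the printed formula. In the correct one it multiplies n by 2.59/4 = 0.6475, a fall of 35%.

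**5. Like-for-like comparison.** One measurement per patient at two-sided 0.05/3 needs 2f = 25.7, so 26 evaluable and 29 enrolled per arm. The figure to set beside 67 is thus 29, not 20.

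**6. What 67 per arm provides.** Less 10% dropout, 67 × 0.9 = 60.3, so about 60 evaluable. At two-sided 0.05/3:

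- Four-time average: SE = 1.55 × √(2 × 2.59/(4 × 60)) = 0.228. Power for 1.40 is above 99.9%. The difference detectable with 80% power is (2.394 + 0.842) × 0.228 = 0.74 points.
- Single time point: SE = 1.55 × √(2/60) = 0.283. Power for 1.40 is 99.5%. The difference detectable with 80% power is 0.92 points.

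**7. Sensitivity to ρ.** With 60 per arm, power for 1.40 on the average stays above 99% for ρ from 0.3 to 1. At ρ = 1 repetition adds nothing, and power is still 99.5%.

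**The case against.** The strongest reply is that the error is on the safe side. The 80% is given as a desired power, and a design with more than 99% meets it. The analysis, the estimates and the error rate do not depend on the sample-size formula. All of this stands, and it limits the point to a correction of a stated figure and its derivation.

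Three stronger readings are tempting, and the documents do not support them.

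- **That the trial is underpowered or misses its 80% target.** The opposite holds on the plan's own inputs.
- **That the repeated-measures step explains the whole rise from 20 to 67.** Section 2.10 also applies Bonferroni and dropout, which alone take 20 to 26 and then 29. The contradiction remains, but it lies between 29 and 67.
- **That a significant but clinically small result is likely.** That depends on the true effect, for which the article gives no basis. The arithmetic shows only that such a difference is detectable.

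It can also be said that 16.6 and 0.74 are conditional. They are: section 2.11 lets QIC choose the correlation structure and allows a gamma model with a log link, under which a difference in VAS points does not carry over directly. The finding of ample power for 1.40 is less fragile, since it also holds at a single time point and over a wide range of ρ.

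Finally, the matter cannot be left to a separate analysis plan, because the article itself prints the formula, the inputs and the result.

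**Conclusion.** The point holds as a should-fix correction. The formula in section 2.10 is not the one for the overall two-group difference in section 2.4; it overstates n by a factor of 4.26 and moves in the opposite direction to the text when measurements are added. Separately, 67 does not follow from that formula at the stated two-sided level, which leads to 79.

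The consequence is an unsupported and generous sample size: 67 enrolled per arm against 19 for the time-averaged contrast, or 29 for a single time point. It does not create a risk of missing 1.40 points. The figures rest on the plan's SD, correlation and dropout rate, a normal approximation, an identity link, exchangeable correlation and two-sided 0.05/3.

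**What to change.** Rewrite the paragraph in section 2.10:

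- Replace the formula with n = 2(Z1−α/2 + Z1−β)² σ² [1 + (κ−1)ρ] / (κΔ²), and state that the level is two-sided 0.05/3.
- Keep 1.40 as the planning difference and give the resulting n: 17 evaluable, 19 enrolled per arm.
- If 67 per arm is kept, label what it provides as a property of the chosen size, not as the design rationale. With about 60 evaluable per arm, under an identity link and exchangeable correlation, that is above 99.9% power for 1.40 points on the four-time average (99.5% at one time point), and 80% power for about 0.74 points (0.92 at one time point).
- Because differences well below 1.40 can reach significance, add to section 2.11 that the estimated difference and its confidence interval will be reported against 1.40.

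The cost is one rewritten paragraph and one added sentence. No change to enrolment is needed.

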### Statistical analysis

2.11

The normality of continuous variables will be assessed using the Shapiro–Wilk test. Data following a normal distribution will be reported as mean (standard deviation, SD), while non-normally distributed data will be presented as median (interquartile range, IQR). Binomial variables will be expressed as proportions. A generalized estimating equation (GEE) model will be used to analyze repeated measures of continuous variables, including VAS scores, QoR-15 scores, maximum walking duration, and subjective sleep quality, accounting for within-subject correlations. The correlation structure will be selected based on the quasi-likelihood under the independence model criterion (QIC). Data distribution will determine the use of either a normal or gamma distribution with identity or log-link functions. *Post hoc* pairwise comparisons will be Bonferroni-corrected. Continuous variables measured at a single time point, such as hospital stay and sufentanil consumption, will be analyzed using *t*-tests or Mann–Whitney U tests depending on normality. Categorical data will be analyzed using the *χ*^2^ test, with *p*-values adjusted using the Bonferroni method and set at 0.017 for pairwise comparisons. Statistical significance will be defined as *p* < 0.05.

All study outcomes will be analysed in the modified intentiontotreat population, including all patients who undergo randomisation with relevant data available. Patients will be included in the analysis according to their original allocation. Multiple testing corrections for secondary outcomes will not be applied; therefore, these outcomes should be interpreted as exploratory findings. Odds ratios (OR) and corresponding 95% confidence intervals (CI) will be reported where appropriate. No interim analysis will be planned. Missing data will not be imputed. Statistical analyses will be performed using SPSS (version 25.0; IBM SPSS). A two-sided *p*-value < 0.05 will indicate statistical significance, except where false discovery rate (FDR) corrections apply.

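### The 67 per group does not follow from the printed formula and inputs, which give 79; it matches exactly only if the Bonferroni alpha is not halved, though this does not show the trial to be underpowered

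*Protocol article*

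**What the plan says.** Protocol article, section 2.10 (Sample size calculation), builds the number in two steps.

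- **First step.** It opens with "Using a two-sided significance level" of 0.05 and "a desired statistical power of 80" percent. The target is "a minimum change of at least 1.40 in the VAS pain score", with a standard deviation of 1.55. It reports "the initial sample size calculation based on a" t-test as 20 per group.
- **Second step.** It brings in four repeated measurements and an intraclass correlation of 0.53. For three pairwise comparisons it reports "adjusting the significance level from 0.05 to 0.017 (0.05/3"). It prints a formula whose quantile term is "Z1-\alpha /2+Z1-\beta", that is, with alpha halved. The result reads: "After adjusting for repeated measures, Bonferroni correction, and an anticipated dropout rate of 10%, we determined that a sample size of 67 participants" per group, 201 in total.

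Section 2.11 (Statistical analysis) says that post hoc pairwise comparisons are Bonferroni-corrected, and that "A two-sided *p*-value < 0.05 will indicate statistical significance". One-sided testing is mentioned in neither section.

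**The concern.** Every input to the final figure is printed and legible, so a reader should be able to repeat the calculation and arrive at 67. That reader arrives at 79. The gap of 12 per group, 36 in all, is too large to be rounding.

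What is at stake is the credibility of the sample size justification. The article presents 67 as the product of a two-sided calculation at the Bonferroni level with 80% power and 10% dropout. The stated method does not return that number, so the stated power for 67 enrolled has no valid derivation behind it.

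**Working it through.** **Inputs, all from section 2.10.** κ = 4 measurements, ρ = 0.53, σ = 1.55, Δ = 1.40, power 80% (z = 0.8416), dropout 10%, α = 0.017 (0.05/3), two-sided.

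**Printed formula.** n = (z₁₋α/₂ + z₁₋β)² × (1 + (κ − 1)ρ) × σ² / (Δ² × (1 − ρ)).

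The part that does not depend on alpha is 2.59 × 2.4025 / (1.96 × 0.47) = 6.2225 / 0.9212 = 6.755. So n = (z + 0.8416)² × 6.755, rounded up, then divided by 0.9 and rounded up again.

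| Alpha used | z | n | Evaluable | Per group with 10% dropout |
|---|---|---|---|---|
| Two-sided 0.017, as stated | 2.387 | 70.4 | 71 | 78.9 → **79** |
| Two-sided 0.05/3 | 2.394 | 70.7 | 71 | 78.9 → **79** |
| Two-sided 0.05, no Bonferroni | 1.960 | 53.0 | 54 | 60 |
| 0.017, not halved | 2.120 | 59.3 | 60 | 66.7 → **67** |
| 0.05/3, not halved | 2.128 | 59.6 | 60 | 66.7 → **67** |

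If dropout is added by multiplying by 1.1, the two-sided 0.017 result is 71 × 1.1 = 78.1, so 79 again.

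**Initial figure of 20.** The normal approximation 2(z + 0.8416)² × 1.55² / 1.40² gives 19.2, so 20, at two-sided 0.05. At one-sided 0.05 it gives 15.2, so 16. The first step therefore fits a two-sided level and the final step does not. The agreement is approximate: an exact two-sided t-test has 79.5% power at 20 per group and needs 21.

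**Does the mismatch mean too few patients?** The printed formula differs from the usual one in three ways. It has no factor 2 for a difference between two groups, it does not divide by κ, and it has (1 − ρ) in the denominator. It raises the evaluable number from 20 to 60 or 71, although the same section says that repeated measurements increase power.

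The standard result for the difference between two groups in the mean of four exchangeable measurements, on the plan's own values, is:

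- Variance of one patient's mean: 1.55² × (1 + 3 × 0.53) / 4 = 2.4025 × 2.59 / 4 = 1.556.
- n = 2 × (2.394 + 0.8416)² × 1.556 / 1.96 = 16.6, so 17 evaluable per group at two-sided 0.05/3, and 17 / 0.9 = 18.9, so 19 enrolled.
- With 60 evaluable, Δ divided by its standard error is 1.40 / √(2 × 1.556 / 60) = 6.15. Power is Φ(6.15 − 2.394), above 99.9%.
- At a single time point with 60 evaluable, the ratio is 1.40 / √(2 × 2.4025 / 60) = 4.95. Power is about 99.4% by t-test (99.5% by normal approximation).

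**The case against.** **The cause is inferred.** The article nowhere says that a one-sided quantile was used, and other routes reach 67. A two-sided form with a factor 2 and without (1 − ρ), 2(z + 0.8416)² × 2.59 × 2.4025 / 1.96, gives 66.2 to 66.5, so 67, but leaves no room for dropout. Two-sided 0.05 without Bonferroni gives 54, then 60, and a second dropout allowance makes 67. Each contradicts something in the text: the first the printed formula and the 10% allowance, the second the Bonferroni step and a single dropout allowance. The unhalved alpha changes one thing and fits exactly, so it is the most likely explanation. It remains an explanation, and only the failure to reproduce is established.

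**A reader might infer that power is 72%.** Putting 60 evaluable into the printed formula at two-sided 0.05/3 gives Φ(√(60/6.755) − 2.394) = 0.72. That value inherits the non-standard variance term and is not the trial's power. For the same reason, 79 per group is what the printed method returns, and is not a number the trial needs.

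**A reader might also infer that the decision rule is unclear**, because the unhalved 0.017 corresponds to a two-sided level of about 0.033. The article does not support this. Section 2.11 sets two-sided p-values and Bonferroni-corrected pairwise comparisons, and the alpha used for sizing does not alter that rule.

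**Conclusion.** The concern holds as an error of derivation. The printed formula and inputs give 71 evaluable and 79 per group, while the article states 67. A quantile with alpha not halved reproduces 67 exactly and is the likely source, but the article does not document it.

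The size of the discrepancy is 12 per group (36 in total) within the plan's own method. It does not extend to a claim that the trial is underpowered: a standard calculation leaves a wide margin at 60 evaluable per group. That reassurance rests on the plan's assumptions of σ = 1.55, Δ = 1.40 and ρ = 0.53, on exchangeable correlation, and on a group contrast that averages the four time points. The single-time-point result does not need the last two or ρ. The point should be corrected because the justification of the primary sample size cannot be repeated. It changes no enrolment number and no testing rule.

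**What to change.** Keep 201 patients and the two-sided, Bonferroni-corrected pairwise rule. In section 2.10, redo the calculation at two-sided 0.017 using the variance of the group contrast that the planned GEE will estimate. Replace the printed derivation with that calculation, and state the resulting power for 67 enrolled and 60 evaluable per group. Do not restate the power as 72%, because that would put a second figure from the same unsuitable formula into the protocol.

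The cost is one corrected calculation and sentence, with no extra patients and no change to the analysis.

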### Statistical analysis

2.11

The normality of continuous variables will be assessed using the Shapiro–Wilk test. Data following a normal distribution will be reported as mean (standard deviation, SD), while non-normally distributed data will be presented as median (interquartile range, IQR). Binomial variables will be expressed as proportions. A generalized estimating equation (GEE) model will be used to analyze repeated measures of continuous variables, including VAS scores, QoR-15 scores, maximum walking duration, and subjective sleep quality, accounting for within-subject correlations. The correlation structure will be selected based on the quasi-likelihood under the independence model criterion (QIC). Data distribution will determine the use of either a normal or gamma distribution with identity or log-link functions. *Post hoc* pairwise comparisons will be Bonferroni-corrected. Continuous variables measured at a single time point, such as hospital stay and sufentanil consumption, will be analyzed using *t*-tests or Mann–Whitney U tests depending on normality. Categorical data will be analyzed using the *χ*^2^ test, with *p*-values adjusted using the Bonferroni method and set at 0.017 for pairwise comparisons. Statistical significance will be defined as *p* < 0.05.

All study outcomes will be analysed in the modified intentiontotreat population, including all patients who undergo randomisation with relevant data available. Patients will be included in the analysis according to their original allocation. Multiple testing corrections for secondary outcomes will not be applied; therefore, these outcomes should be interpreted as exploratory findings. Odds ratios (OR) and corresponding 95% confidence intervals (CI) will be reported where appropriate. No interim analysis will be planned. Missing data will not be imputed. Statistical analyses will be performed using SPSS (version 25.0; IBM SPSS). A two-sided *p*-value < 0.05 will indicate statistical significance, except where false discovery rate (FDR) corrections apply.

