**Methods:**

This single-center, open-label, randomized controlled trial will enroll 201 adult parturients undergoing lower segment transverse cesarean section. Participants will be randomized in a 1:1:1 ratio into three groups (*n* = 67 each): Group LB will receive bilateral quadratus lumborum block with liposomal bupivacaine under ultrasound guidance. Group R-P will receive bilateral quadratus lumborum block with ropivacaine in combination with patient-controlled intravenous analgesia. Group P will receive standard patient-controlled intravenous analgesia without regional nerve block. The primary outcome is postoperative pain intensity, assessed using the Visual Analogue Scale during standardized movement at 12, 24, 48, and 72 h postoperatively. A generalized estimating equation model will be used to assess the overall effect of treatment group on pain scores over time. Secondary outcomes include patient-reported Quality of Recovery-15 scores at 24 and 48 h postoperatively; Visual Analogue Scale for pain at rest, measured at 12, 24, 48, and 72 h postoperatively; need for rescue analgesia; postoperative anxiety (assessed by Visual Analogue Scale at 72 h); subjective sleep quality; maximum walking duration; patient satisfaction with analgesia; incidence of nausea and vomiting; postoperative sufentanil consumption and length of hospital stay. Safety outcomes include allergic reactions, wound infection, lightheadedness, headache, circumoral numbness, tongue paresthesia, drowsiness, irritability, blood pressure fluctuations (hypotension, hypertension), respiratory depression (hypoventilation), and cardiac events (bradycardia, tachycardia, arrhythmia, cardiac arrest). Data will be analyzed using a modified intention-to-treat approach.

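### A stepwise rule for the three primary pairwise comparisons would keep 5% familywise error and never reject less than the planned Bonferroni at 0.05/3

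*Protocol article*

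**What the plan says.** Section 2.4 (Primary outcome) uses a GEE model to "evaluate overall differences in pain scores among groups across the four predefined postoperative intervals", and the abstract describes its purpose as to "assess the overall effect of treatment group on pain scores over time". Section 2.11 (Statistical analysis) then states that post hoc "pairwise comparisons will be Bonferroni-corrected". Section 2.10 (Sample size calculation) carries the same correction into the design: "we applied the Bonferroni correction, adjusting the significance level from 0.05 to 0.017 (0.05/3"). The explicit level in section 2.11, "set at 0.017 for pairwise comparisons", stands in the sentence on chi-square tests of categorical data, but 0.05/3 is clearly meant for the primary pairs too.

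Two things are not said. No sentence makes the pairwise tests conditional on a significant overall test. No sentence says whether each pair is one contrast over the four time points or is read separately at 12, 24, 48 and 72 h.

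**The concern.** Single-step Bonferroni allows for any number of the three pairwise null hypotheses being true at once. With three groups that is more than logic permits: if two pairs are equal, the third must be too. So either all three nulls are true, or at most one is. Once one pair has been declared different, the remaining pairs do not need the divisor of 3 to keep familywise error at 5%.

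What is at stake is power for the second and third comparisons. The Discussion names LB v P and LB v R-P as the two key questions. If LB v P is large and LB v R-P is modest, the second question carries the whole cost of the unused error allowance. That LB v R-P is the smaller difference is plausible, because R-P combines a block with PCIA, but it is an assumption; the protocol gives no figure for it.

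**Working it through.** **Inputs (section 2.10).** SD 1.55, four measurements, ICC 0.53, difference 1.40, two-sided tests, 67 per group with 10% dropout: 67 × 0.9 = 60.3, so about 60 evaluable per arm.

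**Plan's level.** 0.05/3 = 0.0167, written 0.017. The two-sided critical value is 2.394, against 1.96 at 0.05.

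**Standard error of one contrast per pair.** The variance of a woman's four-measurement mean is 1.55² × (1 + 3 × 0.53)/4 = 1.556. The SE of a difference between two arms is √(2 × 1.556/60) = 0.228.

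**Why the stepwise rule is valid.** If all three nulls are true, an error needs the smallest p-value to fall below 0.05/3, which has probability at most 5% by Bonferroni. If exactly one null is true, it is never tested at a level above 0.05. Exactly two true nulls cannot occur. Any p-value below 0.05/3 is rejected under both rules, so the stepwise rule never rejects less than Bonferroni.

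**Familywise error**, simulated from three independent arm means with this SE:

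| Rule | All three equal | Two equal, third far away |
|---|---|---|
| Bonferroni at 0.05/3 (plan) | 4.4% | 1.7% |
| Shaffer step | 4.4% | 5.0% |
| Pairs at 0.05 after a significant 2-df overall test | 5.0% | 5.0% |
| Pairs at 0.05 with no gate | 12.2% | 5.0% |

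**Power for LB v R-P when LB v P is 1.40:**

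| True LB v R-P difference | Bonferroni | Shaffer step | Gain (points) |
|---|---|---|---|
| 0.4 | 26% | 42% | 16 |
| 0.5 | 42% | 59% | 17 |
| 0.6 | 60% | 75% | 15 |
| 0.7 | 75% | 87% | 12 |

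For example, at 0.5 the noncentrality is 0.5/0.228 = 2.2. Power is Φ(2.2 − 2.394) = 42% at 0.05/3 and Φ(2.2 − 1.96) = 59% at 0.05. The gap between the two levels peaks at 17.2 points, at noncentrality 2.18, so 17 is a ceiling.

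**Dependence on the third arm.** At a difference of 0.5, the Shaffer rule raises power from 42% to about 45% if P lies midway between LB and R-P, and to about 49% if P equals one of them: gains of about 2 and 7 points.

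**At the planned 1.40.** Power is 99.99% at 0.05/3 and 99.99% at 0.05; on a single time point it is 99.5% against 99.9%.

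**One contrast per pair matters.** If one truly null pair is tested at 0.05 at each of the four time points, with correlation 0.53, the chance of at least one false positive is about 15%.

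**The case against.** A reader might infer something stronger: that Bonferroni is stacked on an overall test that already protects the pairs by closure, so that it is redundant and gains nothing. The documents do not support that reading.

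- **No gate is written.** The words post hoc suggest an order, not a condition. As the text stands, Bonferroni is the only control on the pairs, and simply dropping it would raise familywise error to about 12%.
- **Bonferroni does lower actual error**, to 1.7% against 5.0% when two arms are equal. It is unnecessary only relative to the 5% target.
- **A gate is not uniformly better.** With the third mean midway, the 2-df statistic equals the pair's z². A pair with z between 2.394 and √5.991 = 2.448 passes Bonferroni but fails the gate.
- **Closure covers one contrast per pair**, not pairs read at each time point.
- **The largest gain arises well below 1.40**, the difference the plan calls clinically significant, and only if the third arm lies far away.
- **Bonferroni is prespecified, valid and consistent** between sections 2.10 and 2.11, and its intervals match its tests. That is useful, because the Discussion also asks whether LB does about as well as R-P.

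All of this stands, and it rules out calling the plan wrong. It does not count against the Shaffer rule as a replacement: that rule needs no gate, keeps the 5% limit and rejects whatever Bonferroni rejects. Only the loss of matching intervals remains as a real cost.

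**Conclusion.** This is a cheap efficiency gain and not an error. The planned Bonferroni tests are valid but more conservative than a 5% familywise target requires with three groups. Replacing them by the Shaffer step adds at most about 17 points of power for LB v R-P (42% to 59% at a difference of 0.5, with P far away), about 2 to 7 points at that difference when P lies midway or equals one of the pair, and practically nothing at 1.40.

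These figures assume SD 1.55, ICC 0.53, 60 evaluable per arm, complete measurements and one contrast per pair averaged over the four time points. The statement about 1.40 uses the standard variance of that contrast. The formula printed in section 2.10 implies a noncentrality at 60 per arm of only √(60/6.755) = 2.98, where 6.755 = (1 + 3 × 0.53) × 1.55²/(1.40² × 0.47). On that basis, 1.40 would have 72.1% power at 0.05/3 and 84.6% at 0.05. That formula divides by (1 − ICC), not by the number of measurements, and has no factor 2 for two arms, so it is not used here.

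**What to change.** In section 2.11, for the primary outcome only:

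1. Define one contrast per pair: the difference between two groups in movement VAS over the four time points, from the GEE model. Label comparisons at single time points as descriptive.
2. Replace Bonferroni for these three contrasts, for example: *The smallest of the three p-values is compared with 0.05/3; if it is significant, the other two are each compared with 0.05 (Shaffer's procedure for three groups). No overall test is required first.*
3. If pairs at 0.05 after a significant overall GEE group test are preferred, write that condition explicitly and restrict it to the same three contrasts.

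The sample size need not change, because every Bonferroni rejection is kept. The cost is a few lines of text, settled before outcome data are seen. Bonferroni simultaneous intervals will no longer correspond one for one with the tests, so the plan should say which intervals will be reported. Keeping Bonferroni as it is would also be defensible.
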